### Secondary outcome: Suicide attempts

As suicide attempts and suicidal ideation are among the strongest predictors of completed suicide [1, 12], these two measurements are taken into account in the analysis as well. To evaluate whether SUPREMOCOL leads to a reduction in suicide attempts in association with the stepwise implementation of the system intervention in the subregions of the province (hypothesis 2), the secondary outcome is the rate of attempted suicides in the subregions of Noord-Brabant. This will be evaluated during the stepped wedge trial. The number of suicide attempts will be estimated based on two measurements: 1) the number of ambulance rides that took place after a suicide attempt, which will be provided by the PHI (GGD Brabant-Zuidoost; Ambulancezorg Zuidoost-Brabant) and the regional ambulance transport (Regionaal Ambulancevervoer Brabant Midden-West-Noord), and 2) on the basis of police registrations as provided by the police. The police registrations comprise E14 reports, which are records of incidents for which the police arrived due to an “attempted suicide”.

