### Pillar 2: providing swift access

Providing swift access to people registered in the monitoring system by specialist crisis teams of SMHIs is the second pillar of our intervention. The first time period after someone showed suicidal behavior remains very vulnerable for relapse, as suicide occurs mostly in people not receiving mental health care [7, 8] and in transitions of and discharges from care [10, 11]. But although suicide risk is thirty times higher in people with a previous attempt [1], one attempt may not necessarily be followed by another one, if proper mental health care is provided after the attempt. Suicide risk can also abate after a failed attempt. Out of 515 patients who attempted suicide at the Golden Gate Bridge, 94% did not die from suicide, at a 26 years follow-up [28]. Moreover, it has been found that appropriate pharmacological or psychotherapeutic treatment may prevent suicide [15, 29]. A recent systematic review and meta-analysis indicated that suicide prevention interventions were found to be effective in preventing completed suicides [30]. Providing swift access to people identified with suicidal behavior to specialist mental health care is thus highly desirable. In this study, swift access will be facilitated by the monitoring system and will be provided by the SMHI. In case a persons’ suicidality is not mainly caused by a psychiatric disorder, but for example, due to financial or somatic problems, the person might be referred to other (health) care settings if that is more appropriate.

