**Fig. 4 Fig4:**
[figure not shown]
Sequential rollout of the suicide prevention system (shaded cells) to the clusters

In our SWTD, the implementation of SUPREMOCOL is sequentially rolled-out to five clusters, until eventually the system is implemented in the whole province. For this purpose, the province is divided into five sub-areas that are based on the service areas of the five participating SMHI’s. The SMHI and a few participating organizations are exposed to the experimental condition from the start of their cluster, but at various time points, more organizations in that cluster may participate if they sign up for participation [40].

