The evaluation of Reach, Efficacy, Adoption, and Implementation will take place during implementation, in the SMHI areas that are allocated to SUPREMOCOL. Evaluation of these domains will be specified per SMHI area and per SWT period (which all last three months). The evaluation of Maintenance will take place nine months after the implementation period, will also last three months and will be evaluated for all SMHI areas separate, as is presented in Table 3. Each dimension is represented on a 0% (no impact) to 100% (most optimal impact) scale. The final Impact score is the function of these five dimensions, calculated for each SMHI region and SWT period [43].

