#### Statistical methods

To examine whether SUPREMOCOL leads to a reduction of completed suicides of 20% in the province of Noord-Brabant, the total number of completed suicides in the post-measurement will be compared to the total number of completed suicides in the pre-measurement. As the total number of residents in this province might have changed, we will also compare the pre- and post-incidence rates of suicides. An exact rate ratio test will be used. To take general trends over time into account, we will compare the incidence ratio in Noord-Brabant with the incidence ratios in other provinces in Noord-Brabant, and with the other provinces combined.

To examine whether SUPREMOCOL leads to a reduction of completed suicides and suicide attempts in association with the stepwise implementation of the system intervention in the subregions of the province, the total number of completed suicides and suicide attempts in each month will be compared to the two levels of our stepped wedge trial: region and time. A poison multilevel model will be used. The occurrence of completed suicide or admissions due to suicide risk in an SMHI will also be taken into account in the analysis. The suicide rates will be corrected for seasonal fluctuations [45]. In a second model, organisational differences between the regions, such as available number of crisis departments, will be taken into account. In a third model, the level of treatment integrity per subregion will be taken into account as well.

To explore whether SUPREMOCOL leads to a reduction of suicidal ideation in people registered in the monitoring system, the scores on the PHQ-9, SIDAS, and decision aid -that will be filled out by participants during the year that they receive the Supremocol additional care- will be compared by repeated measures. This will be used as exploratory process evaluation, as there is no control group for this.

To examine the impact of SUPREMOCOL with regards to reach, efficacy, adoption, implementation, and maintenance, an impact score will be calculated for each SMHI region and time period. This scores will be based on the function of all five RE-AIM dimensions, which are represented on a 0% (no impact) to 100% (best possible impact) scale [43].

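### The stepped wedge Poisson model states no allowance for overdispersion or region-specific change over time, and the attempt outcome draws on two record sources with no combination rule, so standard errors may be too small

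*Protocol article*

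**What the plan says.** All references are to the protocol article.

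- **Outcome.** Under 'Secondary outcome: Suicide attempts', "the secondary outcome is the rate of attempted suicides in the subregions of Noord-Brabant". The section adds: "The number of suicide attempts will be estimated based on two measurements". These are "the number of ambulance rides that took place after a suicide attempt", supplied by two regional ambulance providers, and police E14 incident reports. The section gives no rule for combining them.
- **Model.** Under 'Statistical methods', monthly totals of suicides and of attempts "in each month will be compared to the two levels of our stepped wedge trial: region and time", and "A poison multilevel model will be used" (a misprint for Poisson). A seasonal correction is planned. A second model adds organisational differences between regions, and a third adds treatment integrity.
- **Design.** Under 'Stepped wedge trial design', "the implementation of SUPREMOCOL is sequentially rolled-out to five clusters". Under 'Public health impact', evaluation is "per SWT period (which all last three months" each.

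The article does not mention overlap between the two record sources, overdispersion, or a region-by-time term.

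**The concern.** A Poisson model takes the variance of a count to equal its mean, given the effects in the model. Three things would make the real variance larger:

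1. Adding the two sources when some attempts are in both.
2. Repeat attempts by the same person that fall close together in time.
3. Regions whose underlying rates move differently from one period to the next.

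A region level absorbs stable differences between regions, and a time level absorbs changes that all regions share. Neither absorbs the third item.

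The article gives grounds to expect such movement. Organisations may join a cluster at various times ('Stepped wedge trial design'). Other prevention initiatives, gatekeeper training and staffing changes run alongside the trial ('Potential limitations of the study').

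At stake is a falsely precise stepped wedge result, and so a false positive conclusion about attempts or suicides. For a given amount of regional movement, the distortion grows with the size of the counts.

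**Working it through.** **Figures in the plan.** The article gives no attempt count, overlap share, repeat rate or dispersion, so there is no stated figure to reproduce for this point. The 184 events per year under 'Sample size' belongs to the province-wide pre-post comparison and is not used here. The documented inputs are 5 regions, 3-month periods, 365 suicides in 2017 and, for the primary outcome, a two-sided alpha of 0.05. The rest is assumed and marked so.

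**1. Summing overlapping sources.** Let distinct attempts be Poisson with mean μ, and let a share o be counted twice. The sum has mean μ(1+o) and variance μ(1+3o), so variance/mean = (1+3o)/(1+o).

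| o (assumed) | variance/mean | true SE / Poisson SE |
|---|---|---|
| 0.2 | 1.6/1.2 = 1.33 | 1.15 |
| 0.5 | 2.5/1.5 = 1.67 | 1.29 |
| 1.0 | 4/2 = 2.00 | 1.41 |

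**2. Effect on a nominal 5% test.** True error = 2·[1 − Φ(1.96/√φ)], where φ is the dispersion.

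- φ = 1.25: 1.96/1.118 = 1.753, error 0.080
- φ = 1.5: 1.96/1.225 = 1.600, error 0.110
- φ = 2: 1.96/1.414 = 1.386, error 0.166

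**3. Simulation with no treatment effect.** The set-up was 5 regions, 6 quarters of 3 months, one region crossing over per quarter after the first, a between-region SD of 0.2 (log scale), and a Poisson model with region and quarter effects. Volumes of 20 and 60 attempts per region-month are assumed.

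| Scenario (assumed) | true SE / model SE | type I error |
|---|---|---|
| No overlap, repeats or regional movement | 0.99–1.02 | 0.04–0.05 |
| Sources summed, 20–50% in both | 1.16–1.29 | 0.09–0.13 |
| 0.1–0.3 extra attempts per index attempt, same month | 1.11–1.25 | 0.08–0.12 |
| 30% overlap plus 0.2 repeats | 1.37–1.38 | 0.15–0.16 |
| Region-by-quarter SD 0.1–0.2 | 1.30–2.92 | 0.12–0.50 |

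**4. The same design at the documented suicide volume.** With equal regions, 365/(12×5) = 6.1 suicides per region-month. For a region-by-quarter SD of 0.1 to 0.2, type I error is about 0.06 to 0.15. At ten times that volume (assumed) it is about 0.27 to 0.52. Separate runs differ by a few hundredths; for example, 0.23 to 0.27 at ten-fold volume and SD 0.1.

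**5. Does a random region intercept help?** No. At ten-fold volume and SD 0.1, error was 0.23 with fixed region effects and 0.23 with a random intercept. At SD 0.2 it was 0.52 and 0.51. At the suicide volume and SD 0.2 it was 0.14 and 0.13.

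**6. What repairs it?** Dispersion scaling on monthly counts handles overlap and same-month repeats (0.047 in the combined scenario), but leaves 0.10 to 0.26 under region-by-quarter variation. A quasi-Poisson analysis of region-by-quarter totals with a t reference gives about 0.05. Its degrees of freedom are 30 cells − (5 region + 5 period + 1 treatment) = 19.

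**The case against.** The strongest reply is that the document does not show the standard errors to be wrong. Much of that reply stands.

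- **A reader might infer a plain Poisson model.** The article says multilevel, so stable differences between regions are modelled. The full random-effects structure is not given and could contain a region-by-time term.
- **A reader might infer that the sources are added.** The article numbers them 1 and 2 and never says they are summed. Analysed separately or de-duplicated, they contribute no overlap inflation. The 0.17 figure needs both summation and complete overlap.
- **A reader might infer that repeat attempters always inflate the variance.** Stable differences between people in attempt rate do not: a simulation gave a variance/mean of 1.02. Only repeats that bunch in time do. The statement that "suicide risk is thirty times higher in people with a previous attempt" concerns death by suicide and is not evidence of bunching.
- **A reader might infer that five regions alone shrink the standard error.** With no regional movement the error is 0.04 to 0.05.
- **Dispersion handling often sits in an analysis plan,** which is not shown here. Its absence from an article is not an error in itself.

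What remains is what the article does fix: one attempt rate built from two sources without a rule, and a named Poisson model with only region and time as levels. The planned adjustments do not fill the gap. A seasonal correction removes a pattern shared across regions, and stable organisational differences between regions are the kind a region level already absorbs. Neither addresses region-specific change.

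**Conclusion.** The point holds in conditional form. The stepped wedge standard errors may be too small if the two attempt sources are summed, if repeats bunch in time, or if regions change differently over time. If none of these applies, the test keeps its nominal level.

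The size ranges from a type I error of 0.08 at a dispersion of 1.25 to 0.17 at 2. With a region-by-quarter SD of 0.1 to 0.2 it is about 0.06 to 0.15 at the suicide volume and 0.27 to 0.52 at ten times that volume. The overlap shares, repeat rates, attempt volumes and regional SDs are all assumptions. That attempts are more frequent than suicides is also assumed. The simulated regional deviations were independent between quarters; slow, persistent drift was not examined.

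The firmest part is the missing rule for combining ambulance and police records, because it leaves the secondary outcome itself undefined. The matter is worth correcting before analysis. It does not touch the primary pre-post comparison.

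**What to change.** 1. State that ambulance and police series are analysed separately, or are linked and de-duplicated into one count. State that they are not summed.
2. Replace the Poisson variance with one that allows for region-by-period variation, for attempts and for the stepped wedge analysis of suicides. Either of these serves:
   - a **random** region-by-period effect. A fixed one would absorb the treatment effect, because treatment is determined by region and period;
   - a quasi-Poisson or negative binomial model on region-by-quarter totals, with fixed region and period effects and a t reference (about 19 degrees of freedom with 5 regions and 6 quarters).
3. Do not rely on dispersion scaling of monthly counts alone.

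The change needs a few sentences and standard software. The price is wider intervals. With no excess variation the widening is small and comes mainly from the t reference. With excess variation, the intervals widen roughly by the factor by which the Poisson standard errors were too small, and power falls accordingly.

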### Exploratory process measure: suicidal ideation

To evaluate whether SUPREMOCOL leads to a reduction in suicidal ideation in people registered in the monitoring system, if possible, suicidal ideation will be measured by PHQ-9 and SIDAS questionnaires via an online survey. This will be measured at baseline and after 3, 6, 9 and 12 months. Suicidal ideation will also be measured by the PHQ-9 and decision aid outcomes as filled out in the monitoring system at registration, and during the monitoring contacts at 6 weeks, and 3, 6, 9 and 12 months after registration. For the latter, no extra actions from the person are requested as these questionnaires are already filled out for regular care. The Patient Health Questionnaire-9 (PHQ-9) is a reliable and valid clinical and research tool for the measurement of depression severity [26]. The Suicidal Ideation Attributes Scale (SIDAS) is a valid measure for severity of suicidal ideation [45]. Questionnaires will be as short as possible to promote participant retention and complete follow-up; the PHQ-9 questionnaire consists of nine questions and the SIDAS of five questions.

### Exploratory process measure: suicidal behaviour in SMHI patients

Suicidal behaviour in SMHI patients will be measured and taken into account in the analysis of the stepped wegde trial. It will be measured by SMHI records about the number of completed suicides among their patients and admissions into their institution due to suicide risk. The measurement period will take place during the stepped wedge trial and will be collected for each SMHI.

### Public health impact

The impact of the intervention will be evaluated in terms of the five dimensions - Reach, Efficacy, Adoption, Implementation, and Maintenance - of the RE-AIM framework [43]. All dimensions will be evaluated for each of the four pillars of SUPREMOCOL, which are 1) developing and implementing a monitoring system with decision aid to support professionals in reporting, assessing and monitoring people at risk for suicide, 2) providing swift access to people registered in the monitoring system by specialist crisis teams of SMHIs, 3) positioning of nurse care managers to collaborate with psychiatrists in assessment, case management, and guidance to treatment according to the collaborative care model, and 4) providing telephone monitoring at five fixed times during 1 year to people registered in the monitoring system to enhance adherence to treatment. The RE-AIM dimensions and the variables for the SUPREMOCOL study are presented in Table 2.

**Table 2 Tab2:** Dimensions and definitions of the RE-AIM framework with variables and data sources

Dimension & definition	SUPREMOCOL pillar	Variable	Data source
Reach			
“Proportion of the target population that participated in the intervention” [43]	Pillar 1: monitoring system	• The number (+ characteristics) of chain partners that collaborate in the system versus the number of chain partners that have been approached for collaboration	• Monitoring system • Project group logs
		• The number (+ characteristics) of SMHI’s that collaborate in the system versus the number of SMHI’s that have been approached for collaboration	• Monitoring system • Project group logs
	Pillar 2: swift access	• The number of SMHI’s which are considering swift access versus the total number of participating SMHI’s	• Project group logs • SMHI
	Pillar 3: collaborative care	• The number of SMHI’s which are considering to work according to the collaborative care model versus the total number of participating SMHI’s	• Project group logs • SMHI
	Pillar 4: 12 months follow up	• The number of SMHI’s which are considering to provide 12 months follow up versus the total number of participating SMHI’s	• Monitoring system • SMHI
Efficacy			
“Success rate if implemented as in guidelines; defined as positive outcomes minus negative outcomes” [43]	Pillar 1: monitoring system Pillar 2: swift access Pillar 3: collaborative care Pillar 4: 12 months follow up	• Changes (both positive and negative) in primary and secondary outcome measures (suicidal behaviour), as described in the Methods section	• National and regional health records • PHQ-9 • SIDAS • Monitoring system
		• Experiences of patients and professionals regarding facilitating or hindering factors, as described in the Methods section	• Online surveys • Regular meetings
Adoption			
“Proportion of settings and practices that will adopt this intervention” [43]	Pillar 1: monitoring system	• The number (+ characteristics) of chain partners that made use of the monitoring system versus the number of chain partners who have received an account to this system	• Monitoring system
		• The number (+ characteristics) of SMHI professionals that made use of the monitoring system versus the number of SMHI professionals who have received an account to this system	• Monitoring system
	Pillar 2: swift access	• The number of SMHI departments that have the intention to provide swift access versus the total number of participating SMHI departments	• SMHI
	Pillar 3: collaborative care	• The number of SMHI nurses that have the intention to work according to the collaborative care model versus the total number of SMHI nurses in the SMHI treatment departments	• SMHI
	Pillar 4: 12 months follow up	• The number of SMHI professionals that have the intention to provide follow up contacts versus the total number of SMHI professionals who received an account to the monitoring system	• SMHI
Implementation & Maintenance			
Implementation “Extent to which the intervention is implemented as intended in the real world” [43] Maintenance “Extent to which a program is sustained over time” [43] *Implementation and Maintenance comprise the same variables, however, Maintenance will be measured at nine months.*	Pillar 1: monitoring system	• The number of successful registrations in the monitoring system versus the total number of people attempting suicide (and were in need of an ambulance ride)	• Monitoring system • Ambulance records
		• The number of first contacts that actually took place versus the number of eligible persons for a first contact	• Monitoring system
		• The number of days, after the day on which the first contact should have taken place, the SMHI professional tried to contact the registered person	• Monitoring system
		• The number of days, after the day on which the first contact should have taken place, the first contact between the registered person and the SMHI professional actually took place	• Monitoring system
	Pillar 2: swift access	• The number of crisis assessments or psychiatric consults that were provided by the SMHI professionals versus the total number of crisis assessments or psychiatric consults that were indicated	• Monitoring system
		• The number of swift accesses to care that were arranged by the SMHI professionals versus the total number of swift accessses that were indicated	• Monitoring system
		• The number of clinical admissions that were arranged by the SMHI professionals versus the total number of admissions that were indicated	• Monitoring system
		• The number of people that was referred to their general practitioner by the SMHI professionals versus the total number of people that needed to be referred to their general practitioner	• Monitoring system
	Pillar 3: collaborative care	• The number of SMHI professionals that are involved as case managers versus the total SMHI professionals that have an account to the monitoring system	• Project group logs
		• The number of contacts with the general practitioner by the SMHI professionals versus the total of contacts with the general practitioner that were indicated	• Monitoring system
		• The number of contacts with the psychiatrist by the SMHI professionals versus the total of contacts with the psychiatrist that were indicated	• Monitoring system
	Pillar 4: 12 months follow up	• The number of eligible persons for a follow-up monitoring contact versus the number of follow-up monitoring contacts that actually took place	• Monitoring system
		• The number of days, after the day on which the follow-up monitoring contact should have taken place, the SMHI professional tried to contact the registered person	• Monitoring system
		• The number of days, after the day on which the follow-up monitoring contact should have taken place, the follow-up monitoring contact between the registered person and the SMHI professional actually took place	• Monitoring system

The evaluation of Reach, Efficacy, Adoption, and Implementation will take place during implementation, in the SMHI areas that are allocated to SUPREMOCOL. Evaluation of these domains will be specified per SMHI area and per SWT period (which all last three months). The evaluation of Maintenance will take place nine months after the implementation period, will also last three months and will be evaluated for all SMHI areas separate, as is presented in Table 3. Each dimension is represented on a 0% (no impact) to 100% (most optimal impact) scale. The final Impact score is the function of these five dimensions, calculated for each SMHI region and SWT period [43].

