**Methods/design:**

Study protocol. A regional suicide prevention systems intervention is implemented and evaluated by a stepped wedge trial design in five specialist mental health institutions and their adherent chain partners. Our system intervention is called SUPREMOCOL, which stands for Suicide Prevention by Monitoring and Collaborative Care, and focuses on four pillars: 1) recognition of people at risk for suicide by the development and implementation of a monitoring system with decision aid, 2) swift access to specialist care of people at risk, 3) positioning nurse care managers for collaborative care case management, and 4) 12 months telephone follow up. Eligible patients are persons attempting suicide or expressing suicidal ideation. Primary outcome is number of completed suicides, as reported by Statistics Netherlands and regional Public Health Institutes. Secondary outcome is number of attempted suicides, as reported by the regional ambulance transport and police. Suicidal ideation of persons registered in the monitoring system will, be assessed by the PHQ-9 and SIDAS questionnaires at baseline and 3, 6, 9 and 12 months after registration, and used as exploratory process measure. The impact of the intervention will be evaluated by means of the RE-AIM dimensions reach, efficacy, adoption, implementation, and maintenance. Intervention integrity will be assessed and taken into account in the analysis.

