	4. Did you make suicide plans?
	5. Did you attempt suicide?
In life	6. Did you have thoughts of being better off when you were dead or did you wish you were dead?
Clinical impression	7. Is there any acute danger in the behaviour of the person?

Based on the answers of the person, suicide risk is calculated, which can be either high, moderate or low. The suicide risk is estimated as *high* if the person answers ‘yes’ on question 4 or 5, or on both questions 3 and 6, or if question 7 is answered by the clinician with ‘yes’. If the person answers ‘yes’ only on question 3, or only on questions 2 and 6, the estimated risk is *moderate*. The suicide risk is otherwise estimated as *low* risk. This algorithm is visually displayed in Fig. 1. In the monitoring system, a cut-off is used, in which a moderate and high estimated risk are both labelled as ‘increased risk’.

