### Target population

The target population for the intervention are people that present themselves to, or are identified by, a professional of one of the participating institutions by showing signs of suicidal behavior. In this study, suicidal behavior includes both suicidal ideations and actions -preparatory and attempting- that are undertaken with the intention to die [17]. Inclusion criteria for registration in the monitoring system are 1) having a medium to high suicide risk according to the decision aid (see paragraph ‘Framework’ for the decision aid), 2) being a resident of the province of Noord-Brabant, and 3) giving permission to be registered in the monitoring system. People will be excluded if 1) low suicide risk is assessed, 2) they are not living in Noord-Brabant, and/or 3) they do not give consent to be registered in the monitoring system.

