### Step 1: registration in the monitoring system

In our systems intervention, both (mental) health care professionals - such as emergency room physicians, general practitioners or school psychologists - as well as non-health care professionals - such as railway professionals - can signal people at risk and register them in the monitoring system. When participating professionals signal people at risk, they first ask them for permission for registration in the monitoring system (according to the European Union General Data Protection Regulation [GDPR]). When permission for processing personal data is given, professionals who work as a (mental) health care professional perform a suicide risk assessment via the decision aid, which is built-in the monitoring system. The decision aid provides feedback based on the input provided by the persons’ answers on a questionnaire and observations made by the professional. If the suicide risk is *low* according to the decision aid, the person will not be registered and the professional is advised to refer the person to his/her general practitioner. If the suicide risk is *medium* or *high*, the person will be registered in the monitoring system, and their registration is automatically sent to the nearest SMHI, this is based on the postal code of the person who will be registered. Professionals that do not work in (mental) health care do not perform a suicide risk assessment as they are not authorized and trained to do so. They will register people in the monitoring system based on their own estimation. In these cases, the risk assessment will be performed later on by the SMHI crisis care professional who can use the decision aid to do so.

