### Intervention integrity

The integrity of the intervention will be measured during implementation and will be derived from the ‘Reach’, ‘Adoption’ and ‘Implementation’ dimensions of the RE-AIM framework, as can be seen in Table 3. As the integrity of the implementation of the four individual SUPREMOCOL pillars may not equally contribute to the successful implementation of the intervention in total, weight distribution between the four pillars will be applied. The weighing of these four items in the total intervention integrity degree will be determined by the participating SMHI’s and their chain partners of SUPREMOCOL. For this, the study methods for the weighting of fidelity items by stakeholders’ ratings by Oxman and colleagues [46] will be followed. The chain partners will be asked in a meeting to independently rate the relative importance of the variables belonging to the four pillars in successful implementation, by giving a score from 1 to 10 to the four pillars. Mean intervention degree ratings will be calculated, taking into account the weighing of these items.

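### The pillar 1 item in Table 2 divides all registrations by ambulance-attended attempters only, so it is not a proportion, can pass 100%, and can rise without any more attempters being registered

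*Protocol article*

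**What the plan says.** In Table 2, the first pillar 1 item under Implementation & Maintenance is the "number of successful registrations in the monitoring system versus the total number of people attempting suicide (and were in need of an ambulance ride". Its sources are the monitoring system and ambulance records.

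Who can be registered is set out elsewhere in the protocol article:

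- Abstract, Methods/design: "Eligible patients are persons attempting suicide or expressing suicidal ideation".
- Target population: "suicidal behavior includes both suicidal ideations and actions -preparatory and attempting- that are undertaken with the intention to die". The risk criterion for registration is "having a medium to high suicide risk according to the decision aid"; the other two criteria are residence in the province and permission.
- Pillar 1 section: the decision aid rates risk as high on a yes "on question 4 or 5, or on both questions 3 and 6", or on the clinician's answer to question 7. Question 4 concerns plans, questions 3 and 6 concern thoughts, and only question 5 concerns an attempt.
- Step 1, on professionals outside health care: "They will register people in the monitoring system based on their own estimation".

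On use of the item, Public health impact states: "Each dimension is represented on a 0% (no impact) to 100% (most optimal impact) scale". Intervention integrity says that the integrity degree "will be derived from the ‘Reach’, ‘Adoption’ and ‘Implementation’ dimensions of the RE-AIM framework". Statistical methods brings integrity per subregion into a third stepped wedge model.

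**The concern.** The denominator suggests that the item measures what share of ambulance-attended attempters reach the monitoring system. The numerator, as worded, counts every successful registration. People registered for thoughts or plans, or on a railway worker's own judgement, add to the top of the ratio and cannot appear at the bottom.

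This matters because it is the only item in Table 2 that compares registrations with people at risk in the population. The Reach items count chain partners and institutions, and the other Implementation items concern professionals or people already registered. Yet the section Intervention integrity evaluation promises insight into the share of the target population that took part.

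The error may also differ between areas and periods. Organisations may join a cluster at different times (Stepped wedge trial design), so the number of registrations from non-ambulance routes can change with the mix of partners. Area and period are the units for which impact is scored.

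**Working it through.** The article states no figure for this item, so there is nothing to reproduce. The check is of the definition.

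**Inputs.** For one area and period:
- R = all successful registrations (Table 2 numerator).
- A = people whose attempt needed an ambulance (Table 2 denominator).
- c = share of those A people who are registered.
- r = other registrations per ambulance-attended attempter.

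The article gives none of these values. Those below are assumptions chosen to show a range.

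**Formula.** R = cA + rA, so the item as written is R/A = c + r. An item with a matched numerator would be cA/A = c, which cannot exceed 100%.

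**Item as written, c + r:**

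| True share c | r = 0 | r = 0.25 | r = 0.5 | r = 1 | r = 2 |
|---|---|---|---|---|---|
| 0% | 0% | 25% | 50% | 100% | 200% |
| 10% | 10% | 35% | 60% | 110% | 210% |
| 80% | 80% | 105% | 130% | 180% | 280% |

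An area with c = 80% and r = 0 reads 80% and ranks below an area with c = 0% and r = 1, which reads 100%.

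**The same check from the side of the registrations.** Let s be the share of registrations that are ambulance-attended attempters, and set A = 100. The matched item is sR/A.

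| R | As written, R/A | s = 0 | s = 0.1 | s = 0.3 | s = 0.5 |
|---|---|---|---|---|---|
| 50 | 50% | 0% | 5% | 15% | 25% |
| 100 | 100% | 0% | 10% | 30% | 50% |
| 200 | 200% | 0% | 20% | 60% | 100% |

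The results depend only on R/A and s; A = 50 and A = 200 give the same percentages. For a given number of registrations, the item as written does not respond to s at all. It reaches 100% whenever R is at least A.

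**Place in the score.** Counting the Implementation items in Table 2: pillar 1 has 4, pillar 2 has 4, pillar 3 has 3 and pillar 4 has 3, so 4 + 4 + 3 + 3 = 14. The article does not say how the items combine. If all 14 counted equally, which is an assumption, this one would carry 1/14, about 7%, of the dimension.

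**The case against.** Four points can be made for the plan.

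*The scale applies to dimensions, not items.* This is correct. Table 2 also holds four Implementation items measured in days, so some conversion must exist, and an article may leave it to a fuller document. A cap or rescaling could keep the score within 0% to 100%. It would not repair the item, though, because a capped c + r still rises with r and still does not show c.

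*The word successful may mean ambulance-attended attempters who were registered.* That reading would remove the problem and would parallel the next item, which sets first contacts made against persons eligible. But the article does not define the word and nowhere limits the numerator to attempters.

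*The consequence is limited.* This stands. A reader might infer that an area could be scored as fully implemented while missing all its attempters. The article does not support that: 13 other Implementation items remain, and the integrity degree also draws on Reach, Adoption and stakeholder weights for the pillars.

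*The magnitudes are assumed.* This also stands. A reader might infer that most registrations will be ideation-only, or that the item will in fact pass 100%. The article has no counts to show either. Emergency rooms are among the named settings, so the rows with no attempter registered are limiting cases, not predictions.

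**Conclusion.** The concern holds as a defect in the definition of one process item. As written, the numerator is not a subset of the denominator. The item is not a proportion, has no upper bound at 100%, and can rise with non-attempt registrations whatever the number of attempters captured. This rests only on the wording of Table 2 and on registration rules that allow r to be above zero.

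The size of the distortion cannot be established, because the article gives neither registrations nor ambulance-attended attempts by area. The effect on the Implementation score, the integrity degree and the third model is likewise unknown.

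The reach of the problem is the RE-AIM scores, the integrity degree and the third stepped wedge model. It would be wrong to infer that the main results are at risk: the exact rate ratio test of suicides before and after, and the first two stepped wedge models, do not use integrity. The change is worth making but is not critical.

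**What to change.** Reword the item in Table 2:

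1. Restrict the numerator to registered persons with a recorded attempt, taken as a yes on decision-aid question 5, which is completed in the monitoring system. Label the item approximate. Question 5 covers any attempt in the past month, including attempts without an ambulance, so the ratio can still in principle exceed 100%. The answer may also be missing where a non-health professional registered the person and no decision aid was completed afterwards.
2. If person-level linkage to ambulance records is already available, use registered persons with an ambulance-attended attempt in the same area and period, divided by all such persons. This is the fully matched item. It should not be assumed to be cheap: the section on suicide attempts describes ambulance data only as a number of rides, and registration depends on individual permission.
3. If neither is adopted, report the present ratio as a descriptive ratio of counts and keep it out of the 0% to 100% score and the integrity degree.

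In every case, report the other registrations separately, for example as a count per area and period.

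The cost of option 1 is a change of wording and one filter on monitoring-system data. The downside is an approximate item that may be less favourable than the present one.
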